### Intervention

#### IG

Patients in the intervention condition receive a standardized online memory and psychomotor training (MPMI). The training is accompanied by a workbook for home practice and an educational booklet comprising a summary of each session.

The intervention consists of eight interactive online training sessions of 60 min each that are provided in a group of eight to twelve participants once a week. Two trained scientists conduct the training following a written manual implemented in a PowerPoint presentation. A psychologist administers memory training, and a sports scientist instructs psychomotor exercises. Sessions take place using the video communication application Zoom (Zoom Video Communications, San Jose, CA).

Each session follows the same structure and consists of three parts: (1) Introduction with feedback on home practice, a mood scale, and warm-up exercises (10–15 min). (2) The main part comprises psychoeducation, memory, and psychomotor exercises (30–40 min). (3) The final part includes relaxation, mood scale, summary, and home practice instructions (10–15 min). Feedback is always discussed with all participants. The mood scale is assessed individually. Participants are free to share their experiences and mood, or can keep them to themselves. Table 1 summarizes the psychoeducational content and cognitive and psychomotor exercises.

**Table 1 Tab1:** Content of the online MPMI

Module	Psychoeducation	Cognitive training	Psychomotor training
1	Attention and concentration	Color-Word-Test (Stroop-Test)	Breathing exercise, juggling, relaxation—palming
2	Multi-store model part 1: Perception processing, sensory register, mindfulness	Verbal training: name chain, Auditory perception exercise, mind/mental walk	Finger counting exercise, juggling, relaxation—posture exercise
3	Multi-store model part 2: Short-term store	Verbal training: increasing adjectives with neologism, traffic sign recall, anagram	Finger-tapping, juggling, rope-sensation, relaxation—posture/breathing
4	Multi-store model part 3: Long-term store, mnemonic strategies	Visualization techniques: memorizing names by associative mnemonic image, story method	Ball balancing, juggling, 4–6–8-breathing technique
5	Multi-store model part 4: Retrieval strategies	Verbal training: expressions with color names, alphabet pegs, chunking by categorization, repetition with rhythm	Diagonal motion exercises, palming, yoga

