### Sample size

The primary outcome is the change in the alertness as reaction time in milliseconds (without critical stimulus/warning signal) during the intervention (t1–t2). Based on data from a neuropsychological training in a rehab setting [41], a mean difference of 16 ms (SD = 46.5) between the intervention and control group was estimated.

Therefore, sample size was powered to detect a significant difference of 16 ms (SD = 46.5) in the primary outcome between the study groups (2-sided* α* = 0.05, 1−*β* = 0.80) using analysis of covariance (ANCOVA) and adjusting for baseline values. We assumed a *R*^2^ of 0.5 for the regression of the response on only the baseline covariate. Thus, a total of *n* = 136 persons (*n* = 68 per group) is required. We will include *n* = 170 patients (*n* = 85 per group) based on an estimated dropout rate of 20%.

Furthermore, medium between-group effects (*d* = 0.48) on secondary outcomes can be detected (*p* < 0.05, 1− *β* = 0.80). As power to detect smaller between-group effects on secondary outcomes may be lacking, effect sizes and accompanying 95% confidence intervals will be reported throughout. Sample size calculation was conducted in Power Analysis & Sample Size PASS 2020 (NCSS, LLC, Kaysville, Utah; https://www.ncss.com/software/pass) by a statistician from the Institute of Clinical Epidemiology, University of Würzburg.

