## Assignment of interventions

### Randomization and allocation concealment

All participants are randomly assigned to the IG or CG after consent is given and initial assessment and questionnaires (t1) are completed. A block randomization procedure (block size: 2 and 4) with an allocation ratio of 1:1 is used. A member of the Institute of Clinical Epidemiology and Biometry at the University of Würzburg (external randomization) created for each of the eight-session groups a separate randomization list with computer-generated random numbers, which is stored locked at the IKE-B.

Members of the research team are informed about the allocation after the baseline assessment. Therefore, a consecutive list with the participants’ IDs (research codes) of each session group is sent per e-mail to the IKE-B member. Randomization results are added to the IDs and sent back per e-mail afterwards.

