#### Main research question

The primary and secondary endpoints will be analyzed according to the intention-to-treat principle. Treatment effects (between-group effects) will be calculated separately for each follow-up time point using analysis of covariance (ANCOVA) adjusting for baseline values. Statistical significance (*p* < 0.05, two-sided), difference in means with 95% confidence intervals (CI), and effect sizes (ή^2^) will be reported for all outcomes. Furthermore, within-group effects, including standardized effect sizes (SES) and accompanying 95% CI, will be calculated for both study groups. Bonferroni corrections to adjust the significance level for multiple tests are planned within secondary cognitive outcomes. Further secondary outcomes will be analyzed exploratorily without adjustment. A sensitivity analysis is conducted for primary analysis by additionally including the group as random effects in a linear mixed model for the primary endpoint to estimate the effect of the group.

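### IG patients train in shared groups, but the sample size and primary ANCOVA assume independent patients, and the one group-effect check leaves its group term undefined

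*Protocol article*

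**What the plan says.** All references are to the Protocol article.

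- **Delivery (Intervention, IG):** the training is "provided in a group of eight to twelve participants once a week", with feedback and home practice discussed in the whole group. Under CG, controls receive usual care and may join the training only after the last follow-up.
- **Randomisation (Randomization and allocation concealment):** a member of the biometry institute "created for each of the eight-session groups a separate randomization list with computer-generated random numbers". The IDs of a session group are listed first and allocations are added afterwards, so IG and CG patients carry the same session-group label.
- **Sample size:** the trial is "powered to detect a significant difference of 16 ms (SD = 46.5) in the primary outcome between the study groups", with an R² "of 0.5 for the regression of the response on only the baseline covariate", giving 136 analysed and 170 randomised. No ICC or design effect appears.
- **Analysis (Statistical analysis, Main research question):** the primary model is an ANCOVA at each follow-up, adjusted for the baseline value. A sensitivity analysis extends it "by additionally including the group as random effects in a linear mixed model for the primary endpoint to estimate the effect of the group".

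**The concern.** Patients who share sessions, trainers and group discussion may end up more alike than patients from different groups. That correlation can arise through treatment in the IG only. An ANCOVA on independent patients then understates the standard error of the IG-CG difference, so a borderline p-value on alertness looks stronger than it is, and the planned power is an upper bound.

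Session group is also the randomisation stratum, and it is missing from the primary model. That omission works the other way: differences between session groups that both arms share stay in the residual and make the test slightly conservative.

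The sensitivity analysis is the only place where a group effect enters, so whether it protects the primary result depends on what its group term means.

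**Working it through.** **Inputs from Sample size:** difference 16 ms, SD 46.5, R² 0.5, two-sided α 0.05, 68 analysed per arm, 20% dropout. **From Intervention, IG:** 8 to 12 per group. **Assumed, not in the document:** IG ICC of 0.01 to 0.10; IG groups filled by trial IG patients only; equal group sizes.

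**1. The plan's own figure.** Residual SD = 46.5 × √(1 − 0.5) = 32.88 ms. SE = 32.88 × √(2/68) = 5.64 ms, and 16/5.64 = 2.837. Normal-approximation power = Φ(2.837 − 1.96) = 0.81; the noncentral-t version with 133 degrees of freedom gives 0.804. 136/0.8 = 170. The stated figures reproduce under independence.

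**2. Clusters.** 85/12 to 85/8 gives about 7 to 11 IG groups. After 20% dropout, m = 0.8 × 8 = 6.4 to 0.8 × 12 = 9.6 analysed per IG group.

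**3. Clustering in the IG only.** DE = 1 + (m − 1) × ICC. The variance of the difference is inflated by V = (1 + DE)/2.

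- Power allowing for clustering = Φ(2.837/√V − 1.96).
- Type I error of the plain ANCOVA = 2 × [1 − Φ(1.96/√V)].
- Small-sample version: Satterthwaite df = (DE + 1)² / [DE²/(K − 1) + 1/67], with K = 68/m IG groups.

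Example, m = 9.6 and ICC 0.05: DE = 1.43, V = 1.215, power = Φ(2.837/1.102 − 1.96) = 0.73, type I error = 0.075, df about 17.

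| Assumed ICC | V (m = 6.4; 9.6) | Power, normal | Power, Satterthwaite | Type I error, plain ANCOVA |
|---|---|---|---|---|
| 0.01 | 1.027; 1.043 | 0.80; 0.79 | 0.78; 0.75 | 0.053; 0.055 |
| 0.02 | 1.054; 1.086 | 0.79; 0.78 | – | 0.056; 0.060 |
| 0.05 | 1.135; 1.215 | 0.76; 0.73 | 0.73; 0.68 | 0.066; 0.075 |
| 0.10 | 1.270; 1.430 | 0.71; 0.66 | 0.68; 0.60 | 0.082; 0.101 |

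**4. What the sensitivity model does under each coding.** If the group is the session-group label and enters as one random intercept for both arms, that intercept appears in both the IG mean and the CG mean of each session group and largely cancels from their difference. Balanced simulation (7 to 11 session groups, 6 to 10 analysed per arm in each, no session-group variance shared by both arms) gave these type I errors:

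| Model | ICC 0.05 | ICC 0.10 |
|---|---|---|
| Plain ANCOVA | 0.064-0.081 | 0.082-0.105 |
| Shared random intercept | 0.067-0.084 | 0.088-0.109 |
| Session group as fixed stratum | 0.065-0.082 | 0.085-0.109 |
| Partially nested (IG groups as clusters, controls unclustered) | 0.04-0.05 | 0.04-0.05 |
| Session-group-by-arm random effect | about 0.05 | about 0.05 |

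**5. The opposite effect of the stratum.** With 5% of variance shared by both arms of a session group and no IG clustering, the plain ANCOVA has type I error 0.043-0.048. With IG ICC 0.01 added it is 0.046-0.050, so the two roughly cancel. With IG ICC 0.05 it is 0.060-0.072, so the offset is only partial.

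**The case against.** The strongest reply has four parts.

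**The size is unknown.** The ICC is not in the document. The outcome is an individual keypress reaction time, and delivery follows a written manual with observed sessions, which limits trainer-driven differences. This stands: nothing in the article supports 0.10 over 0.01, and at 0.01-0.02 the shift is small. A reader might infer that the stated power and error rate simply fail. The document supports only that they depend on an ICC near 0.

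**The sensitivity model may already be right.** A reader might infer that the planned check certainly misses IG clustering. The article says only that the group enters as random effects. It does not mention an intercept or an effect common to both arms, and a partially nested coding would fit the same sentence and would work. A shared intercept is the likely reading, because the session-group label is assigned before allocation, but it is not the stated one. Coding details may also sit in an analysis plan that is not shown. The sample-size basis and the primary model, however, are stated here, and both assume independence.

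**Cluster-aware models are costly with 7 to 11 clusters.** This stands. At ICC 0.05 simulated power is about 0.67-0.73 with partially nested coding and 0.59-0.67 with a session-group-by-arm term. Keeping the ANCOVA as primary with a well-defined clustered check is defensible.

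**It is late.** Recruitment was due to end in June 2025, follow-up assessors are not blinded, and protocol changes go to the ethics committee. This argues against enlarging the sample and for settling the wording before results are seen.

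**Conclusion.** The point holds in conditional form. The article sets out group delivery in one arm and randomisation by session group, but its sample size and primary model account for neither. With 68 analysed per arm, the flat 80% power is the best case. By the normal approximation it becomes 0.79-0.80 at ICC 0.01, 0.73-0.76 at 0.05 and 0.66-0.71 at 0.10, and it is lower with small-sample degrees of freedom. The plain ANCOVA's error rate is close to 5% at ICC 0.01-0.02 and materially above it from about 0.05. Leaving out the stratum offsets this only partly at ICC 0.05. The sensitivity model is ambiguous, and under its most natural coding it would not detect or correct IG clustering. These sizes rest on the assumed ICC range and on balanced groups made up of IG patients.

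**What to change.** Before any outcome analysis:

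1. **Add session group, the randomisation stratum, to the primary ANCOVA.** This aligns the model with the randomisation. It does not deal with IG clustering, and it removes the slight conservatism of leaving the stratum out, so step 2 is needed with it.
2. **Define the planned mixed model.** State that the group is the session group, with a random effect acting in the IG only (partially nested, controls not clustered by treatment) and Satterthwaite or Kenward-Roger degrees of freedom. Report the IG ICC. Call the primary result robust only if this model agrees with it.
3. **Restate power as a range over ICC 0-0.10** in place of the flat 80%.

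**Cost.** No new data are needed, since session-group membership is already held for randomisation. The changes are analysis wording, with submission to the ethics committee where the protocol text changes. The stated power becomes less favourable, and the IG-clustered interval is clearly wider (at ICC 0.05, power about 0.67-0.73 partially nested, about 0.59-0.67 with a session-group-by-arm term). If session groups also differ in ways both arms share, the partially nested model without the stratum is conservative (type I error about 0.03 at ICC 0.05 with 5% shared variance). Whether the clustered model replaces the ANCOVA as primary is therefore a trade-off for the sponsor, to be fixed before results are seen.

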#### Secondary research question

Moderator analysis will be performed by including the moderator variable as an additional factor or covariate and examining interaction effects. Significance levels for interaction effects will not be adjusted for multiple tests due to their exploratory nature.

We will also use ANCOVA adjusting for baseline values to examine the effect on physical performance.

Furthermore, correlation- and regression analyses between subjective cognitive changes and the changes in cognitive performance tests will be conducted.

### Monitoring

No data monitoring committee (DMC), interim analyses, and auditing were planned. The study team consists of two independent working groups (including biometric expertise) that are committed to ethical standards and the guidelines of “Good research practice”. The study results are reported to the ethics committee. There is no need for a DMC due to short duration, minimal risks, and no treatment restrictions.

Regular meetings of the team members and the principal investigator are implemented to discuss recruitment, assessment, data management, and intervention implementation.

Furthermore, ethical issues are monitored. The risks of harm to participants are minor. However, when dealing with cognitive impairment, cognitive assessment and training may lead to psychological stress. If participants discontinue the assessment or intervention, the reasons (e.g., adverse effects on psychological well-being) are documented by the study team members. A serious adverse event (SAE) is suicidality and suicide, which may or may not be causally related to study participation. SAEs will also be documented and immediately reported to the principal investigator.

### Ethics, consent and permissions

The study conformed to the principles of the Declaration of Helsinki. The Ethics Committee of the University of Würzburg approved the study protocol on 10.11.2021 (reference number: 173/21). All changes to the study protocol will be submitted to the Ethics Committee for approval. Participation in the study is voluntary and based on written informed consent. Eligible participants will be informed about all relevant aspects of the study, in particular, that participation in the study is voluntary and that they can withdraw their consent at any time without incurring any disadvantages.

The study team members will publish this study protocol and study results; there are no publication restrictions.

#### Patient or public involvement

Patients were not involved in the development of the study. However, feedback on the group program will be collected during the study. Furthermore, after the trial concludes, lay-language summaries will be disseminated to participants to ensure they are informed of the results. The study results will also be presented at informational events for patients. Patient perspective will be used to revise the MPMI before dissemination.

## Discussion

Cancer-related cognitive problems can significantly impact the quality of life for individuals undergoing cancer treatment and during survivorship. Non-pharmacological interventions that have shown benefits in addressing subjective or objective cognitive impairment include CT, CBT, meditation/MBSR, and exercise training. However, more research is needed to explore various cancer types, the timing of interventions, self-reported and objective outcome measures, and long-term follow-up to determine the most effective interventions and identify the patient subgroups that benefit the most.

In this RCT, we will evaluate the short- to intermediate-term effectiveness of a combined online memory and psychomotor intervention compared to usual care for cancer patients experiencing subjective cognitive impairment. Additionally, we will explore treatment effects related to specific subgroups.

Methodological challenges may arise due to the online training format, training adherence, the extensive data collection at three measurement appointments over 6 months, and the need to account for multiple potential confounders.

Overall, the results of this study will enhance our understanding of the effectiveness of a combined online memory and psychomotor intervention in both subjective and objective cognitive outcomes. If the MPMI shows positive effects, it should be implemented in psycho-oncological routine care.

## Trial status

This trial is at protocol version 6, dated 28.07.23. Date of first enrollment: 19.12.2023. Recruitment will be completed at the end of June 2025.

## Data Availability

Only the research team will have access to the final data set and statistical code; there are no data sharing plans. However, this study protocol will be published and made publicly available. In addition, the trial protocol and further materials (in German) will be available upon reasonable request by contacting the corresponding author.

## Abbreviations

6MWT: 6-Minute walk test
CCCMF: Comprehensive Cancer Center Mainfranken
CG: Waiting control group
CRCI: Cancer-related cognitive impairment
CrF: Cancer-related fatigue
CRF: Case report form
DSM-IV: Diagnostic and Statistical Manual of Mental Disorders
EORTC: European Organization For Research and Treatment of Cancer Quality of Life Questionnaire
FACT-Cog: Functional Assessment of Cancer Therapy—Cognitive Function
GAD-7: Generalized Anxiety Disorder scale
IG: Intervention group
MPMI: Memory and psychomotor intervention
PCI: Perceived cognitive impairment
PHQ-9: Patient Health Questionnaire-9
QLQ-C30: Quality of Life Questionnaire Core 30
QLQ-FA12: Quality of Life Core Function Questionnaire
RCT: Randomized controlled trial
SAE: Serious adverse event
t1: Baseline assessment
t2: Post-intervention assessment
t3: Follow-up assessment
TAP: Test Battery of Attentional Performance
TMT: Trail making test
VLMT: Verbal learning and memory test
